#### Statistical analysis plan

2.3.6

Caregiver sensory evaluation scores obtained through Likert-type or hedonic scales will be treated as ordinal data. Summary statistics will be presented as medians and interquartile ranges. Differences in sensory preference scores across THR recipes will be assessed using non-parametric tests, including the Kruskal-Wallis test, as appropriate. Changes in acceptability and adherence scores across repeated TIPs cycles will be analyzed using the Friedman test.

Qualitative analysis will be performed by thematic coding of barriers and caregiver feedback. Content analysis of qualitative responses on cultural appropriateness and ingredient feasibility will be done.

### Phase III: cluster randomized controlled trial to assess the effectiveness of the intervention package

2.4

#### Study design and setting

2.4.1

A parallel two-arm, multi-centre cluster randomized controlled trial will be conducted in the six districts, each located in a different state, as outlined earlier, to evaluate the effectiveness of an intervention package including improved THR and SBCC strategies compared to the existing THR and SBCC strategy on the nutritional status of children aged 6–36 months. Areas within these districts where formative research or phase two activities have taken place will be excluded.

The effectiveness of the intervention package will be assessed at two levels:

(1) Individual (and household) level, focusing on children aged 6–36 months with special emphasis on the6-24 months age group, the critical window for growth and development.

(2) Population level, focusing on children aged 6–36 months.

A cluster randomized controlled trial (cRCT) will consist of two components to document the effectiveness at two levels, as mentioned above:

Individual level outcome—Longitudinal (cohort) approach: to study changes in the outcome indicators at an individual level in children aged 6–36 months. Eligible children aged 6–18 months will be recruited and followed for 18 months after initiation of the intervention, who turn 24–36 months old by the end of follow-up.Population level outcome—Repeated cross-sectional approach: to study changes in the outcome indicators at the population level among children aged 6–36 months. All eligible children aged 6–36 months residing in the study area will be assessed at baseline, then at 6-month intervals (6, 12, and 18 months) and an endline at 24 months of initiation of the intervention implementation.

A schematic overview of phase 3 is illustrated in Figure 4.

**Figure 4 fig4:**
[figure not shown]
Schematic overview of the phase 3.

#### Study unit and clusters

2.4.2

In the study, anganwadi centres (AWCs) will serve as the unit of implementation. Considering the location of the AWCs in close proximity and the presence of multiple AWCs in the same village, which may pose a risk of contamination, Health Sub-Centres (HSCs)/Health and Wellness Centres (HWCs) will serve as the proxy unit for selecting the clusters (AWCs) and randomization. In each district, HSCs/HWCs will be randomly selected from the multiple blocks, with the number of HSCs/HWCs to be sampled from each block proportionate to the population of each block. A minimum of two blocks will be selected in each study district following discussions with government stakeholders. Requisite number of HSCs per block will be sampled using random number tables, ensuring representation across urban, rural, tribal, and diverse geographic constituencies. Under each selected HSC, one to two AWCs (depending on the population size, covering about 1,000 population to ensure availability of the desired number of children) will be randomly selected to form the study clusters.

To be eligible for inclusion, AWCs that are functional with both anganwadi worker (AWW) and anganwadi helper (AWH), actively available, will be considered. AWCs that are contiguous or located in hard-to-reach areas will be excluded.

#### Study participants

2.4.3

All the children aged 6–36 months who live in the selected AWC area, registered with the AWC and regardless of their socioeconomic status, will be eligible to receive the THR and SBCC, according to the allocation arms. The quantity of THR that they will receive will be based on ICDS guidelines, considering both their age and nutritional status (normal, MAM, or SAM). There are no exclusion criteria. For the children not registered in the AWCs, the caregivers and household head will be counselled for registration in the AWC.

##### Eligibility of the children for individual-level outcome assessment (cohort component)

2.4.3.1

Here, children under two years of age, belonging to the critical window of the first 1,000 days, will be targeted. Specifically, children aged between >6 and <18 months, of any gender and socioeconomic background, will be included. Eligibility will require that the child resides within the selected AWC area and is likely to remain there for the study duration, is registered with the AWC, and has a family willing to receive THR and SBCC services through the designated AWC. Children will be excluded if they have major congenital malformations or medical/surgical conditions (known/as reported by parents) that interfere with dietary intake, or if consent for participation is denied.

In each selected AWC, at least 10 children will be identified based on the eligibility criteria. Only one child per household shall be included in the outcome assessment. If more than one child in the eligible age group is available in the selected household, the younger child will be considered. It is anticipated that recruitment of the desired children across the clusters may take about 2–4 months. The primary outcome documentation for the cohort has been proposed at 18 months, expecting that the children aged 18 months will turn 36 months at the time of endline assessment.

##### Eligibility of children for population-level outcome assessment (cross-sectional component)

2.4.3.2

Universal sampling will be employed for the cross-sectional component. All children aged 6–36 months living in the study area (AWC), of any gender and socioeconomic background, who are present during the survey, regardless of their AWC registration status and THR or SBCC usage, will be included in the repeated cross-sectional surveys. Children will be excluded if they have major congenital malformations or medical/surgical conditions (known/as reported by parents) that interfere with dietary intake, or if consent for participation is denied.

#### Intervention

2.4.4

The intervention package will comprise an improved THR product and an SBCC strategy as prepared in phase 2. The improved THR will be prepared by an identified self-help group (a type of community-based organization), vendor, or manufacturer, based on the finalized composition of THR, cost considerations, and necessary regulatory approvals.

The intervention will be delivered primarily by anganwadi workers and anganwadi helpers from the ICDS system, supported by the Implementation Support team. Additionally, Accredited Social Health Activists (ASHAs), Auxiliary Nurse and Midwife (ANMs) from health functionaries will complement the efforts in intervention clusters as per need. Supervisory support will be provided by ICDS/Women and Child Development (WCD) and health officials at the block and district levels.

Participants in comparator clusters will continue to receive existing THR products and SBCC services as per the ongoing ICDS program without any change in composition and delivery.

Services in the intervention versus comparator arms are described in Supplementary Table 2.

#### Study outcomes

2.4.5

The data for the longitudinal (individual-level outcome) and cross-sectional (population-level outcome) study components will be collected simultaneously at baseline (pre-intervention), and then at six-monthly intervals; i.e. at 6, 12, 18 and 24 months (endline). For the longitudinal or cohort component outcomes, the data collected at baseline, months 6, 12 and 18 months of intervention will be used to assess the key outcome and the trend in the cohort. Although the intervention will be implemented over 18 months, follow-up will continue until the endline at 24 months post-baseline. This extended follow-up period is aligned with the independent expert committee’s recommendations and allows for a more comprehensive assessment of the intervention’s effect, as key improvements in growth and nutritional outcomes are more likely to manifest over time.

For the cross-sectional component outcomes, the data collected between the baseline (month 0) and endline (month 24) will be used to assess the outcome and the trend (data at months 6, 12, and 18).

##### Primary outcome

2.4.5.1

Change in weight-for-age z-score (WAZ), based on WHO growth standards, among children aged 6–36 months enrolled in the longitudinal component of the study, measured between baseline and 18 months of follow-up.

###### Secondary outcomes

2.4.5.2

For children aged 6–36 months enrolled in the longitudinal component: nutritional status based on WAZ, HAZ, WHZ, and MUAC, IYCF practices, dietary and nutritional intake, water, sanitation and hygiene (WASH) practices, and health status.For children aged 6–36 months assessed under the cross-sectional component: nutritional status based on WAZ, HAZ, and WHZ, and acceptance and usage of THR.Other outcome indicators- Cost-effectiveness of the intervention: The incremental cost-effectiveness of implementing the intervention package will be compared with the existing THR and SBCC strategy in the study district.

Details of the outcome indicators to be assessed in Phase 3 are presented in Supplementary Table 3.

#### Sample size

2.4.6

The sample size is calculated to detect a minimum mean difference of 0.3 in mean WAZ score between intervention and comparator arms, assuming a mean WAZ of −1.8 in the comparator group and a standard deviation of 1.0 in both groups (45, 46). With 80% power, 5% significance level, an intra-cluster correlation coefficient of 0.05, and an expected attrition rate of 20%, the estimated sample size is 300 per arm per site. This will be achieved through 30 clusters per arm, with an average of 10 children per cluster.

#### Randomization and blinding

2.4.7

The unit of randomization will be HSC, as a proxy for the AWC. Sixty HSCs/HWCs from different blocks in the district will be identified using simple random sampling. Under each selected HSC, the eligible AWC, as per the eligibility criteria described in the earlier section, will be selected using simple random sampling for the implementation of study activities. To meet the required number of children in the eligible age groups in areas such as hilly/tribal/sparse habitation, more than one AWC (contiguous AWCs covering about 1,000–1,200 population) may be included, which will be considered as one cluster. For the larger villages/urban areas with more than one AWC, only one AWC (with a population of about 1,000–1,200) will be selected for inclusion in the study. While selecting the AWCs from the HSCs, it will be ensured that the AWCs selected from different HSCs are drawn from areas not involved in pilot studies, non-contiguous, and are located at a reasonable distance to minimize contamination.

Selected HSCs and 60 AWC units (clusters) will be randomized into the two arms by an independent statistician; 30 into the intervention arm and 30 into the comparison arm. Randomization will be stratified by the blocks included, such that every HSC/AWC randomized to the intervention arm will have an HSC/AWC randomized to the control arm from the same block. For randomization, pair matching of clusters will be done considering key parameters such as location stratum (urban–rural) and population size. Within each matched pair, one cluster will be randomized to the intervention arm and the other to the comparison arm. Within each selected AWC, 10 children will be randomly sampled from all eligible children in the cluster.

The allocation sequence will be generated by an independent statistician. The allocation code for each of the 60 clusters will be available only to the statistician and shared with the site investigator upon request, ensuring allocation concealment.

While blinding of investigators and participants to the intervention allocation is not possible, the data analysts will not be aware of the two study arms. There will be two separate study teams in the field that will be independently working: (1) an Implementation Support Team (IST) responsible for supporting the implementation of the planned packages in the intervention clusters, including training, supervision, product supply, monitoring, and periodic surveillance. The team will provide on-site support to anganwadi workers, document process indicators, and report any unintended negative outcomes. During field visits, team members will also interact with caregivers at the households and community members to understand their response and challenges; (2) Outcome Assessment Team (OAT) will be responsible for outcome assessment. The OAT will function independently of the IST, with restricted opportunities for interaction, and will be masked to intervention and comparison arms to minimize bias. The team will identify eligible households and conduct anthropometry measurements and data collection every six months (at baseline, 6, 12, 18, and 24 months) using appropriate tools for outcome assessments in both intervention and comparison clusters.

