##### Sociodemographic data

2.4.9.6

Background characteristics of study participants, including the demographic and socioeconomic status, family members, reproductive and morbidity history of the mother, will be collected using a structured questionnaire (adapted from the National Family and Health Survey-5 household tool). The age of the child will be calculated based on the date of birth recorded from the birth certificate/record/discharge record. In the absence of any official birth records, the date of birth as reported by the mother/primary caretaker will be used. The socioeconomic status of the households will be captured using the Kuppuswamy scale.

In addition, a random sample of THR products will be analyzed for nutrient composition and bacterial content in NABL-accredited labs.

The participant timelines of data collection and analyses for different components are summarized in Table 3.

**Table 3 tab3:** Participant timelines (53) outlining enrollment, interventions, and scheduled assessments in Phase 3.

Activities and data components	Time points					
	Enrollment	Month 0 (baseline assessment)	Month 6	Month 12	Month 18	Month 24 (endline assessment)
Enrollment						
Eligibility screen	X					
Informed consent	X					
Randomization	X					
Intervention/comparator						
Improved THR and SBCC						
Existing THR and SBCC						
Data collection						
I. Longitudinal component						
Socio-demographic information		X				X
Anthropometry indicators (weight, length/height, MUAC)		X	X	X	X	X
IYCF and nutritional practices, household food security		X	X	X	X	X
WASH practices		X	X	X	X	X
Health status		X	X	X	X	X
THR utilization		X	X	X	X	X
II. Cross-sectional component						
Anthropometry indicators (weight, length/height, MUAC)		X	X	X	X	X
THR utilization		X	X	X	X	X
Generic data						
Nutrient composition of improved THR		X				
Data collection for economic evaluation and analysis		X	X	X	X	X

Data collection team (OAT members) will receive rigorous training in anthropometric measurements according to standard protocols, as well as in the administration of study tools and data capture procedures. Additionally, intrarater and interrater reliability testing for anthropometry measurements will be undertaken across sites and data collectors. The data collected will be reviewed periodically to ensure accuracy and reduce missing outcome data.

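### Allocation concealment and assessor masking are claimed, but the release rule and visit procedures described do not ensure either

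*Protocol article*

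**What the plan says.** **Concealment.** Section 2.4.7 (Randomization and blinding) has an independent statistician generate the sequence. The codes for the 60 clusters are "available only to the statistician and shared with the site investigator upon request, ensuring allocation concealment". The same section states that "blinding of investigators and participants to the intervention allocation is not possible".

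**Recruitment of the cohort.** Section 2.4.3.1 says: "It is anticipated that recruitment of the desired children across the clusters may take about 2–4 months". Among other criteria, a child qualifies if the child "is likely to remain there for the study duration" and "has a family willing to receive THR and SBCC services through the designated AWC"; refusal of consent excludes. That section has at least 10 eligible children identified per anganwadi centre (AWC), while section 2.4.7 has 10 drawn at random from all eligible children in the cluster.

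**Order.** Table 3 (section 2.4.9.6) puts eligibility screening, consent and randomization together in the Enrollment column, ahead of the month-0 baseline column.

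**Masking.** Section 2.4.7 says the Outcome Assessment Team, which identifies households and collects all outcome data, "will be masked to intervention and comparison arms to minimize bias". Table 3 lists "THR utilization" beside anthropometry at months 0, 6, 12, 18 and 24 in both the longitudinal and the cross-sectional component. Section 2.4.10 has data collectors work in pairs on both questionnaires and anthropometry.

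**The concern.** A cluster trial needs concealment at two points: when clusters are assigned, and when individual children are identified, judged eligible, consented and measured. The release rule covers the first. It is offered as proof of concealment in general, yet nothing in it covers the second. If the arm is known while eligibility is judged and consent is sought, the two cohorts can differ in ways randomization did not create, and adjustment for measured covariates cannot be relied on to undo that.

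Masking is a separate matter. A team that discusses ration use with caregivers who know what they receive cannot be assumed to remain unaware of the arm. Knowledge of arm can affect length measurement and the probing of recalled feeding and illness.

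**Working it through.** The claim concerns procedure, so the main check sets the sections side by side. A short calculation then shows how sensitive the trial would be to a residual bias.

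**1. Can the arm be known during recruitment?**
- Release: on request, with no time point or condition (2.4.7).
- Recipient: the site investigator, who is not blinded (2.4.7).
- Randomization: before month-0 measurement. Because Table 3 shares one column, its order relative to listing and consent is not fixed.
- Community orientation covers the intervention package and takes place before commencement (2.4.8.1). Worker training precedes roll-out (2.4.8.2). Neither is tied to closure of the cohort list.

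Following the text as written, an investigator may hold the codes throughout the 2–4 months. The text permits this; it does not say that it happens.

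**2. Where does judgement enter?** Random sampling protects only within the frame of eligible children. That frame depends on likely residence, family willingness and AWC registration, and caregivers of unregistered children are counselled to register (2.4.3). Consent also affects who enters.

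**3. Can the assessors learn the arm?** The month-0 THR item precedes the intervention and cannot unmask. From month 6, intervention households hold the improved product and are given printed materials and cookbooks (2.4.8.3), and caregivers are unblinded. No separation of the person measuring from the THR questions is described. Allocation is by cluster, so one disclosure reveals the arm of every child in that cluster.

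**4. Sensitivity to a residual bias (illustration).** The stated sample size is reproduced first, using section 2.4.6: difference 0.3, SD 1.0, two-sided 5%, power 80%, ICC 0.05, attrition 20%.
- Per arm without clustering: 2 × (1.960 + 0.842)² × 1.0² / 0.3² = 174.4, so 175.
- Design effect with 8 children retained per cluster: 1 + (8 − 1) × 0.05 = 1.35.
- 175 × 1.35 = 236.25, so 237; 237 / 0.8 = 296.25, so 297. This agrees with the stated 300 per arm per site, which is not in dispute.

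Standard error of the arm difference, SE = √(2 × 1.35 × 1.0² / n):
- One site, n = 300 × 0.8 = 240: SE = 0.106.
- Six sites pooled, n = 6 × 240 = 1,440: SE = 0.043.

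With a net bias b remaining in the estimated effect, the two-sided type I error is 1 − Φ(1.96 − b/SE) + Φ(−1.96 − b/SE):

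| Assumed b (WAZ) | One site | Six sites pooled |
|---|---|---|
| 0 | 5% | 5% |
| 0.03 | 5.9% | 10.7% |
| 0.05 | 7.6% | 21.1% |
| 0.10 | 15.6% | 63.7% |

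The values of b are assumptions. The SE uses the planning SD of WAZ and ignores pair matching and the correlation between baseline and follow-up. The table shows only that a large pooled sample makes small biases matter.

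**The case against.** Much of the case on the other side stands.

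- **Clusters are protected.** They are selected and matched into pairs before randomization, so concealment at cluster level is not shown to fail.
- **Discretion is limited.** Ten children are drawn at random, and households are identified by a team kept apart from the implementation team and meant to be masked. The codes go to the site investigator, not to that team.
- **The incentive to select is weak.** Every registered child aged 6–36 months in the area receives that arm's ration and communication (2.4.3), so cohort entry brings no extra access. The willingness criterion applies in both arms.
- **The primary outcome is a change.** It is the change in WAZ to 18 months (2.4.5.1), analysed with a time-by-group interaction (2.4.11). A stable entry difference largely drops out; only differing trajectories would bias it.
- **Both arms receive THR.** Whether the utilization item reveals the arm depends on its wording, which is not shown. Electronic scales, reliability testing and 5% repeat collection by supervisors also help.

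A reader might infer that codes will be released while recruitment is under way, or that concealment and masking have failed. The text leaves the timing open and supports neither. A reader might also set an entry shift against the target: 20% of children replaced by others 0.5 WAZ different gives 0.20 × 0.5 = 0.10, a third of 0.3. Both inputs would be invented, and most of a stable shift would cancel in the change.

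What remains is that the stated release rule does not support the concealment claimed for it, and that masking is asserted more firmly than the visit procedures allow. The first is not detail left to a fuller document: the article states the rule and draws a conclusion that does not follow.

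**Conclusion.** The point holds as a gap between claim and procedure. Concealment during listing, consent and baseline measurement is not ensured, because release of the codes has no time condition. Masking after baseline is not ensured, because the assessors collect THR utilization from caregivers who know what they receive.

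No bias size can be derived from the documents. For the primary outcome the exposure is probably modest, since a stable entry difference largely cancels and weight on an electronic scale leaves little room for assessor influence. Length, and hence LAZ/HAZ and WHZ/WLZ, and recall-based feeding and morbidity outcomes are more exposed. The point should be settled before clusters are randomized, because biased recruitment cannot be dependably repaired in analysis. The sample size is unaffected.

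**What to change.** **Section 2.4.7, release of codes.** Replace the on-request rule with a time lock: the statistician releases the codes for a matched pair only after eligibility listing, random sampling, consent and baseline measurement are complete in both clusters of that pair. Baseline here includes the cohort assessment and the simultaneous cross-sectional survey. Release comes before any arm-specific training or sensitisation in those clusters.

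**Sections 2.4.3.1 and 2.4.7, sampling.** State one procedure: list all eligible children, then draw 10 at random.

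**Section 2.4.7, masking.** Describe masking of the Outcome Assessment Team as attempted. At each visit do anthropometry before the THR and feeding modules, and record the assessor's guess of arm.

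**Cost.** No extra children are needed. Training and supply in a pair start only once its baseline is closed, so roll-out is slightly staggered, and joint training sessions and monthly supply need planning around that. Measuring first protects only partly, because one disclosure unmasks a cluster for later children and visits. The recorded guesses will show how far masking held but will not restore it.
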